## Abstract

**Background:**

Immigrants are known to experience greater socioeconomic stress and poorer well-being and to suffer more from lifestyle- and diet-related disorders than native populations. There is also evidence that children of immigrant parents are at greater risk of diverse health problems than their host country cohorts. The aim of this study is to apply and evaluate the efficacy of an early life intervention program among parents/children with immigrant background to prevent childhood caries and obesity, thereby improving the children’s general health, oral health, and quality of life.

**Methods:**

This is a study protocol for a cluster randomized controlled intervention follow-up study. In phase I of the study, the primary care health centers in the municipality of Bergen, Norway were randomly allocated to intervention or control groups. The intervention was carried out using the motivational interviewing technique and the common risk factor approach. The intervention group received guidance on diet/oral hygiene and the control group received standard care information. Parental knowledge and children at age 3 and 5 years old will be assessed in a prospective phase II follow-up study compared to native Norwegian controls. The primary outcome will be evaluation of change on parental oral health related knowledge and attitudes. The secondary outcome will assess the impact of the intervention on children’s caries -, body mass index- and oral health related quality of life.

**Discussion:**

Collaboration between dental public health and primary health care personnel on the common risk approach motivational intervention offers opportunities to address key dietary behaviors that may prevent obesity and dental caries. Providing sustainable preventive measures decreases the burden of diseases and consequently reduces health inequalities, particularly among at-risk children.

**Trial Registration:**

The study is registered as a clinical trial (ClinicalTrials.gov Identifier: NCT05758454: 7 March 2023). Ethical approval has already been granted by the Regional Ethical Committee (REK) (2015/ 27,639 /REK vest) and Sikt – Norwegian Agency for Shared Services in Education and Research (Reference number 778825).

**Supplementary Information:**

The online version contains supplementary material available at 10.1186/s12903-023-03329-9.

## Background

According to Statistics Norway [1], immigrants comprise nearly 20% of the population. They represent health-, societal- and economic assets, but also face challenges which the Norwegian society might help to address, facilitating their adaptation and integration to the new culture. A Norwegian of immigrant background is a person born in Norway, with one or two immigrant parents. Immigrants tend to find their changed living conditions disorienting, making it difficult for them to participate fully in the new society. For many reasons, a move to an unfamiliar environment may be difficult, not least due to lack of proficiency in the language of the new country. Several studies confirm that compared to the native population, the well-being of immigrants in Norway is poorer and they suffer more from lifestyle and diet-related disorders such as obesity [2–5].

Food security describes a situation in which there is physical, social, and economic access to safe, nutritious food, in quantities which meet the dietary needs and food preferences required to ensure an active and healthy life [6]. Food insecurity is reported to affect the well-being of children and adults of immigrant families in many Western countries, including the United States and United Kingdom [6, 7]. For most migrants, both the number of calories and the content of the diet change as a result of diverse factors, including language difficulties, lack of acculturation, shortages of previously used products, and culturally related factors associated with food. These factors underlying dietary changes may all contribute to different diseases, including a higher risk of obesity, type 2 diabetes, and cardiovascular disease as well as dental caries. Kumar and co-authors reported a high prevalence of obesity and overweight among immigrants from Pakistan and Turkey [5]. Studies primarily from the United States and United Kingdom have consistently shown that upon arrival, immigrants have lower BMI than their host-country-born counterparts. After longer residence, however, there is a change to higher BMI, overweight and obesity [8]. Compared with ethnic majority children in Denmark, Norway, and Sweden, non-western (NW) immigrant children show overall poorer health outcomes with respect to diabetes, obesity, oral health, mental health, and well-being [9]. A recent review of meta-analyses of data from studies conducted in developed and developing countries revealed that overweight and obese children had significantly more dental caries than children of normal weight [10]. In the sample population, both conditions were found to be associated with low levels of parental income and education [11]. Some immigrant groups who transition from a fiber-rich, whole grain diet to a high-fat diet with lower vegetable intake might be at increased risk of diabetes and cardiovascular disease [5]. A previous report has revealed that specific dietary habits (frequent intake of sugar and sweetened drinks) were considered to be common risk factors for both childhood obesity and caries [12].

In addition to dietary habits which constitute risk factors common to obesity and dental caries, other habits uniquely associated with heightened caries risk are common among immigrants. In some immigrant communities toothbrushing, oral hygiene routines and preventive dental care are less common and not regarded as important [13, 14]. Many families seek dental care only when a child is in pain or there is visible decay and preserving baby teeth may not be prioritized [15]. A Norwegian cohort study identified the following significant caries risk indicators among children at age 5 years: a mother consuming a diet very high in fat or sugar, a mother with low education and one or both parents of NW immigrant background [16].

Early childhood caries (ECC) is defined as any form of caries (cavitated or non-cavitated) occurring in the primary dentition of children aged 6 years or younger [17]. In children aged between 2.5 and 3.5 years, a combination of different factors constitutes predictors for developing caries, including the mother’s education, immigrant background, and consumption of candy and sugar-containing beverages [18].

In high-income countries there has been a marked decline in the incidence and prevalence of ECC over recent decades, reducing the psychosocial and economic burden of this disease for individuals and for society [19]. However, ECC remains an important health issue in particular population subgroups and in many countries, including Norway, immigrant children are found to be at high risk. Previous studies have revealed that children of NW immigrant backgrounds have higher caries experience than their native counterparts [17, 20–22]. This is attributed to lack of parental knowledge, poor communication due to language barriers and ethnic and cultural differences.

Children with ECC may experience pain when drinking hot or cold liquids, difficulty chewing and biting, poor appetite, weight loss, disturbed sleep, behavioral changes such as irritability and low self-esteem and a decline in academic achievement [23]. Furthermore, a recent study revealed that ECC has a negative effect on the quality of life (QoL) of preschool children and their families [22]. Further research is needed to determine whether and if so, to what extent, the quality of life of immigrant families living in Norway is affected by their children’s EEC.

Globally, obesity and dental caries constitute increasing public health problems. Both conditions are multifactorial, chronic, and highly prevalent, with significant and potentially lifelong impacts on health and quality of life [24]. The two conditions are thought to share common contributing factors, including biological, genetic, socioeconomic, cultural, environmental, dietary, and lifestyle factors [25]. The dietary factors include poor food choices, unhealthy dietary habits, frequent and high consumption of fermentable carbohydrates, consumption of sweetened foods/drinks, and high-calorie/cariogenic diets [26]. In a previous study, obesity, socio-economic factors, infrequent toothbrushing habits, and consumption of cariogenic beverages were identified as significant caries risk factors. It is of interest to note that a weak association was found between caries and extreme obesity (or morbid obesity) in children aged 4–17 years [20].

Though no evidence emerged of an association between obesity and caries among 6-year-old British children living in Plymouth, the deprivation highlights the vulnerability of children living in disadvantaged families to have both excess weight and more carious lesions [27].With caries and obesity acknowledged as the two most prevalent diseases of childhood, additional research should focus on the benefits and feasibility of widespread interdisciplinary medical-oral health collaboration in addressing and modifying common risk factors [28]. There are few culturally tailored health interventions. The fact that there are risk factors common to several systemic and oral health conditions, would support an approach in which oral health is integrated into primary health care services.

Reduction of free sugars in the diet can be part of a strategy to reduce risk factors common to both dental caries and childhood obesity. Thus, information about family standards, parental attitudes, and dietary habits of parents of NW immigrant backgrounds might provide a valuable tool for planning, implementation, and evaluation of culturally adapted health promotion programs. Intervention programs, focusing on dietary- and oral hygiene practices among NW immigrant families attending primary health care centers and based on a Common Risk Factor Approach (CRFA) and Motivational Interviewing (MI) might successfully reduce the incidence of caries and obesity. Such a program could be implemented within a community-based healthcare system throughout the country. Potentially, the trial results might be extrapolated to fill a knowledge gap about immigrant parents in Norway.

Several approaches for intervention have been applied to establish a model for child oral health promotion and to reduce inequalities in oral health. In a study carried out in Melbourne, families of Iraqi, Lebanese, or Pakistani backgrounds, with children aged 1–4 years, were invited to participate in an intervention project including community oral health education sessions and reorienting of dental health and family services. According to the authors, the findings from this study contribute to the limited evidence base in support of community interventions to improve child oral health in migrant communities [29]. In a recent study among Indian children aged 10–12 years, it was shown that an intervention in the form of oral health education (delivered through lectures and demonstrations by an undergraduate dental student) and topical antibacterial therapy (fluoride varnish and povidone-iodine) resulted in an improvement in caries and periodontal scores [30]. It is claimed that in indigenous communities in Alaska, community-centered multilevel interventions (educating families and communities and training mid-level dental care providers) will improve oral and systemic health and reduce pediatric tooth decay [31].

### Aims

The objectives of this project are:

To investigate the efficacy of a culturally adapted behavioral intervention on knowledge, attitudes, and behaviors related to a child’s risk for dental caries and obesity, with special reference to parents of NW immigrant background, with children aged 0–6 months.To assess the effect of the behavioral intervention on children’s caries increment and family quality of life.To generate research-based information about NW immigrants’ oral health issues, healthcare needs, and utilization of health services.To evaluate possible differences and similarities in oral hygiene and feeding practices among parents of different cultural backgrounds (immigrants and native Norwegians).To monitor parents’ attitudes to their children’s oral health in a follow-up study for children aged 3 and 5 years and to measure the children’s quality of life, body mass index (BMI) and caries status.

## Hypothesis

We hypothesize that compared to ethnic majority parents in Norway, immigrant parents have poor dietary knowledge, deleterious parental feeding habits and caring behaviors which might trigger caries and obesity among their newborn children. Small children of NW immigrant parents receiving common risk dietary interventions and guidance on hygiene/ feeding practices have better health parameters, including fewer carious lesions, standard BMI, and better quality of life than the control group.

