## Methodology

### Trial Design

This is a cluster randomized controlled intervention follow-up study. By integrating primary health care and the public dental health service, the basis of the study is the application of an early-life intervention program among parents/children of immigrant backgrounds, using the MI technique and CRFA to prevent dental caries and obesity, thereby improving their general health, oral health, and quality of life. Primary care health centers in the municipality of Bergen, Norway, were randomly allocated to intervention or control groups (allocation ratio 1:1), to evaluate the efficacy of the culturally adapted dietary/hygiene advice. The intervention group received guidance on diet/hygiene and the control group received standard care, including regular health information at the primary care health centers. The study has been funded by the Norwegian Research Council for three years.

The study has two phases:

**Phase I (The Intervention Study)** involves assessing oral health-related knowledge, attitudes, and behavior among immigrant parents of infants (0–6 months). It also involves investigating the potential of a culturally adapted oral health education intervention to prevent the development of ECC and to improve parental oral health-related knowledge and awareness (Fig. 1).

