### Inclusion criteria

#### Phase I

Immigrant parents (IM) of infants (0–6 months old) with NW background (Eastern Europe, Asia, Africa, Turkey, South and Central America) were recruited from different primary health care centers in the municipality of Bergen, Norway. Before the recruitment phase, the health centers were allocated to either intervention or control groups.

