#### Phase II

The immigrant parents involved in the intervention study (IM) and a new group of parents of Norwegian background (N) will be recruited from similar public dental health clinics when they visit these centers for their children’s routine oral health examinations at the ages of 3 and 5 years.

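### The first hypothesis compares immigrant and native parents on care of newborns, but natives are first assessed at child age 3, and then against an immigrant group that includes intervention recipients

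*Protocol article*

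**What the plan says.** The Hypothesis section opens with a comparison between populations: "We hypothesize that compared to ethnic majority parents in Norway", it says, "immigrant parents have poor dietary knowledge, deleterious parental feeding habits and caring behaviors which might trigger caries and obesity among their newborn children". A second sentence, on intervention versus control, follows and is not at issue here.

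The Trial Design section says that phase I "involves assessing oral health-related knowledge, attitudes, and behavior among immigrant parents of infants (0–6 months" old. The phase I inclusion criteria name the same population: "Immigrant parents (IM) of infants (0–6 months old) with NW background". Under Primary outcome measures, the phase I questionnaires fall at child ages 0–6 and 18–24 months and are completed by the immigrant (IM) parents.

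Native parents appear in the phase II inclusion criteria: "a new group of parents of Norwegian background (N) will be recruited from similar public dental health clinics", at the point "when they visit these centers for their children’s routine oral health examinations at the ages of 3 and 5 years". The abstract agrees, placing the comparison with native controls in phase II at those two ages.

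The section on the data collection instrument says that a questionnaire will be used in both phases. It covers knowledge of breastfeeding and feeding, attitudes, eating habits and oral hygiene.

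The phase II description in Trial Design takes its immigrants from phase I and labels them the test group (IM), against a Norwegian control group (N). The outcomes at 3 and 5 years (caries increment, BMI, quality of life) use the same two labels.

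**The concern.** A comparative hypothesis can be tested only at a stage when both groups are observed. The first hypothesis ties feeding habits and caring behaviors to newborn children, and the design observes only one of the two groups at that stage.

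The comparison that remains, at 3 and 5 years, has its own difficulty. The immigrant parents have by then been through a trial whose purpose was to change the knowledge and habits that the hypothesis describes. A difference between natives and the whole immigrant group would mix background with the effect of the intervention.

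At stake is a negative statement about how immigrant parents care for newborns relative to natives, which the data could neither support nor refute. There is also a risk of understating a real difference at 3 and 5 years.

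**Working it through.** The plan gives no figure for this comparison, so there is none to reproduce. The check sets the schedule out by group and then works through the effect of pooling.

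**Step 1. Who is assessed, and when** (Trial Design, Inclusion criteria, Outcomes)

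| Child age | Immigrant parents (both arms) | Native parents |
|---|---|---|
| 0–6 months | yes | no |
| 18–24 months | yes | no |
| 3 years | yes | yes |
| 5 years | yes | yes |

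The infancy and toddler assessments number two for immigrants and none for natives. Both groups are seen only at 3 and 5 years. The article states no recall question about infancy for native parents.

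**Step 2. What natives are asked.** The instrument is used in both phases, so knowledge, attitudes, eating habits and hygiene are collected from natives at 3 and 5 years. What is missing for them is feeding and care as practiced in infancy.

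**Step 3. Who is in the immigrant group at 3 and 5 years.** The IM group is the phase I population, and centers were allocated 1:1. According to the section on the intervention, one arm had an individual presentation of about 30 minutes, a brushing demonstration and a pamphlet covering diet, bottle feeding and dental visits. These are the topics of the first hypothesis.

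**Step 4. Effect of pooling.** On a scale where higher is better, let
- D = native mean minus control-arm immigrant mean,
- δ = intervention effect still present at the phase II visit,
- p = share of the immigrant group from the intervention arm.

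The pooled immigrant mean is the control-arm mean plus pδ, so

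native minus pooled immigrant = D − pδ.

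The difference shrinks by pδ. The article does not say what δ will be at 3 years, so as an illustration I take the two planning effects from the Sample size section and assume that they persist:
- p = 1/2 (equal arms): 0.5 × 0.25 = 0.125 and 0.5 × 0.15 = 0.075.
- p = 3/7 to 4/7 (the seven centers in the Fig. 3 caption, assumed of equal size): 0.25 × 3/7 = 0.107 to 0.25 × 4/7 = 0.143, and 0.15 × 3/7 = 0.064 to 0.15 × 4/7 = 0.086.

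If the effect has faded by 3 years, δ is near 0 and so is the shrinkage. If it has not, the better the intervention works, the more the pooled comparison understates D.

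**The case against.** The best defense is that the word newborn is loose. It sits in a clause about who might suffer the consequences and sets no visit. The article itself notes that no teeth have erupted at 6 months, so newborns cannot literally have caries. On this view the hypothesis is about parents in general and the phase II questionnaire tests it.

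Part of this stands: the Hypothesis section gives no assessment age. But the same section speaks of small children in its next sentence, and the Theoretical framework section uses newborn for the families whom the intervention targets, which is the phase I stage. The plain reading is therefore early infancy. Even on the loose reading, the undivided immigrant group remains a problem.

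A reader might also infer more than the documents support:
- *That natives are never asked about diet, knowledge or hygiene.* They are, at 3 and 5 years.
- *That aim 4 is contradicted as well.* It compares hygiene and feeding practices across cultural backgrounds without naming a child age, so phase II data can address it.
- *That the plan will set immigrant data at 0–6 months against native data at 3 years.* No section proposes this. The comparisons with natives that carry an age are at matched ages.
- *That the trial's main result is affected.* The primary outcomes concern immigrant parents only, intervention against control, and do not depend on this hypothesis.

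**Conclusion.** The point holds in a limited form. Infancy-stage feeding and care is not measured in native parents, so the first hypothesis as worded cannot be tested. The same topics can be compared at 3 and 5 years, but the article defines the immigrant side of that comparison as a single group containing intervention recipients.

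Under the assumptions above, pooling would take roughly 0.06 to 0.14 off the immigrant–native difference, on the scale of the article's planning effects. That range is illustrative: it depends on the arm shares and on how much of the effect survives to the phase II visits. The direction does not depend on those values, provided that the intervention improves knowledge and habits.

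The conclusion rests on the text alone, because Figs. 1 and 2 are not shown, but the text on recruitment is explicit. A later analysis plan could divide the immigrant group by arm. It could not supply native data from infancy. The change should be made, but the point does not threaten the randomized trial.

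**What to change.** 1. Restate the first hypothesis as a comparison of knowledge, feeding habits and oral hygiene practices between immigrant and native parents at child ages 3 and 5 years.
2. Name control-arm immigrant parents as the immigrant group for this comparison, or report the two immigrant arms separately against natives.
3. State as a limitation that, by age 3, the immigrant parents were due two phase I interviews and the natives none. The article also describes retention measures (health information, a toothbrush and a mouth mirror) without distinguishing arms, so control-arm parents are not wholly unexposed.
4. Leave the wording of aim 4 as it is and read it at the same two ages.

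The cost is rewording plus one line on the analysis group, with no new data. The claim about newborn care is given up, and the immigrant group is smaller for this one comparison. Native recruitment is described in the future tense and recruitment is expected to run to 2025, so on the article's text the change can precede the comparison.

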## Methodology

### Trial Design

This is a cluster randomized controlled intervention follow-up study. By integrating primary health care and the public dental health service, the basis of the study is the application of an early-life intervention program among parents/children of immigrant backgrounds, using the MI technique and CRFA to prevent dental caries and obesity, thereby improving their general health, oral health, and quality of life. Primary care health centers in the municipality of Bergen, Norway, were randomly allocated to intervention or control groups (allocation ratio 1:1), to evaluate the efficacy of the culturally adapted dietary/hygiene advice. The intervention group received guidance on diet/hygiene and the control group received standard care, including regular health information at the primary care health centers. The study has been funded by the Norwegian Research Council for three years.

The study has two phases:

**Phase I (The Intervention Study)** involves assessing oral health-related knowledge, attitudes, and behavior among immigrant parents of infants (0–6 months). It also involves investigating the potential of a culturally adapted oral health education intervention to prevent the development of ECC and to improve parental oral health-related knowledge and awareness (Fig. 1).

